#### Sample size calculations

Sample size calculations are based on the expected effects of the intervention on the primary outcome, quality of life, measured by the SF-12. Calculations are done using the equation for a longitudinal design [34] and adjusted for the effect of clustering of primary care practices [35]; SF-12 coefficients used in the calculations are derived from previous studies with a study population similar to ours. The number of follow up measurements is 4; Mean cluster size is based on the expected number of participants per cluster at baseline (N = 33). We assume the following: a standard deviation of 7.1 (PCS and 6.6 (MCS) [36], a correlation coefficient of repeated measurements of 0.66 (PCS) and 0.5 (MCS) [37], an intra-cluster correlation coefficient of 0.02 for both PCS and MCS [36], an alpha of 0.05 and a power of 90%. To detect a clinical difference of 3 points [29] on the SF-12 scale between intervention and control groups and assuming an attrition rate of 20%, the study would require 180 (PCS) and 131 (MCS) eligible patients per arm.

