**Methods/design:**

In a 2-year stepped-wedge cluster randomised clinical trial with 6-monthly measurements, the chronic care model will be compared with usual care. The trial will be carried out among 35 primary care practices in two regions in the Netherlands. Per region, practices will be randomly allocated to four allocation arms designating the starting point of the intervention. *Participants*: 1200 community-dwelling older adults aged 65 or over and their primary informal caregivers. Primary care physicians will identify frail individuals based on a composite definition of frailty and a polypharmacy criterion. Final inclusion criterion: scoring 3 or more on a disability case-finding tool. *Intervention*: Every 6 months patients will receive a geriatric in-home assessment by a practice nurse, followed by a tailored care plan. Expert teams will manage and train practice nurses. Patients with complex care needs will be reviewed in interdisciplinary consultations. *Evaluation*: We will perform an effect evaluation, an economic evaluation, and a process evaluation. Primary outcome is quality of life as measured with the Short Form-12 questionnaire. Effect analyses will be based on the “intention-to-treat” principle, using multilevel regression analysis. Cost measurements will be administered continually during the study period. A cost-effectiveness analysis and cost-utility analysis will be conducted comparing mean total costs to functional status, care needs and QALYs. We will investigate the level of implementation, barriers and facilitators to successful implementation and the extent to which the intervention manages to achieve the transition necessary to overcome challenges in elderly care.

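### The 180 (PCS) and 131 (MCS) per arm at 90% power come from a two-group parallel formula and do not describe the planned four-sequence stepped wedge of 1200; the mismatch is conservative

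*Protocol article*

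**What the plan says.** The section Sample size calculations names the method: "Calculations are done using the equation for a longitudinal design [34] and adjusted for the effect of clustering of primary care practices [35". Its inputs are:

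- "The number of follow up measurements is 4";
- "a standard deviation of 7.1 (PCS and 6.6 (MCS");
- "a correlation coefficient of repeated measurements of 0.66 (PCS) and 0.5 (MCS");
- an intra-cluster correlation of 0.02, a mean cluster size of 33 and 20% attrition;
- "an alpha of 0.05 and a power of 90"%.

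The target is worded as a two-group contrast, "To detect a clinical difference of 3 points [29] on the SF-12 scale between intervention and control groups", and the result is that "the study would require 180 (PCS) and 131 (MCS) eligible patients per arm".

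The design is set out elsewhere in the article. Study design and setting describes a stepped wedge in 35 practices, measured at baseline and at 6, 12, 18 and 24 months, with all practices on the intervention by the end. Randomisation gives four allocation arms starting at 0, 6, 12 and 18 months. The Abstract plans for "1200 community-dwelling older adults aged 65 or over".

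**The concern.** The sample size section contains no step, crossover or period effect, although the rest of the article relies on the stepped wedge. A formula for two groups that each stay in one condition throughout does not give the power of a trial in which every practice contributes both conditions.

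Three things follow. A reader cannot tell what power the planned trial has, or how small an effect it can detect. The unit of the stated requirement is unclear, because the article otherwise uses arm for the four sequences. And no sentence connects 180 or 131 to 1200. What is at stake is whether the stated justification describes the trial being run.

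**Working it through.** **1. Reproducing the stated figures.** Two-group repeated-measures formula, two-sided alpha 0.05, power 90%:

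n per group = 2 (z₀.₉₇₅ + z₀.₉₀)² SD² [1 + (T − 1)ρ] / (T δ²)

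with (z₀.₉₇₅ + z₀.₉₀)² = 10.507, T = 4 and δ = 3. Multiply by the design effect 1 + (33 − 1) × 0.02 = 1.64 and divide by 1 − 0.20.

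- PCS: 10.507 × 7.1² × 2 × (1 + 3 × 0.66) / 36 = 87.7; × 1.64 = 143.8; / 0.8 = 179.8, so 180.
- MCS: 10.507 × 6.6² × 2 × (1 + 3 × 0.5) / 36 = 63.6; × 1.64 = 104.3; / 0.8 = 130.3, so 131.

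Both match. One-sided alpha gives 147 and 107. T = 5 gives 176 and 126. Multiplying by 1.2 for attrition instead of dividing by 0.8 gives 173 and 126. None of these fits. The article does not call the formula two-group parallel; that is inferred from the double match and from the contrast it names.

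**2. What per arm adds up to.**

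| Reading | PCS total | MCS total |
|---|---|---|
| Two comparison groups (the formula's meaning) | 2 × 180 = 360 | 2 × 131 = 262 |
| Four allocation arms (the article's usual meaning) | 4 × 180 = 720 | 4 × 131 = 524 |

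The plan is 1200, or 300 per allocation arm. Expected yield is 35 × 33 = 1155.

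**3. The planned design.** Each measurement is taken before a start at the same time point. All practices are then in usual care at baseline and all in the intervention at 24 months, so both conditions coexist only at 6, 12 and 18 months. The figure showing practices per arm is not available, so I assume a 9/9/9/8 split. Attrition is applied as 20% fewer patients throughout, so m = 33 × 0.8 = 26.4 per practice.

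The model has fixed period effects and random practice and patient effects. Practice means then have

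- variance SD² [0.02 + 0.98/m];
- covariance between occasions c = SD² [0.02 + (ρ − 0.02)/m].

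Write s for variance minus covariance.

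- PCS: variance 2.879, c = 2.230, s = 0.649.
- MCS: variance 2.488, c = 1.663, s = 0.825.

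The variance of the estimated effect is

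I s (s + T c) / {(I U − W) s + (U² + I T U − T W − I V) c}

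with I = 35 and T = 5. The remaining terms are:

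- U = 9×4 + 9×3 + 9×2 + 8×1 = 89;
- W = 9² + 18² + 27² + 35² = 2359;
- V = 9×16 + 9×9 + 9×4 + 8×1 = 269;
- first bracket: 35 × 89 − 2359 = 756;
- second bracket: 7921 + 15575 − 11795 − 9415 = 2286.

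Putting the numbers in:

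- PCS: 35 × 0.649 × 11.80 / (756 × 0.649 + 2286 × 2.230) = 0.0480, SE 0.219.
- MCS: 35 × 0.825 × 9.141 / (756 × 0.825 + 2286 × 1.663) = 0.0596, SE 0.244.

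The difference detectable at 90% power is 3.2415 × SE: 0.71 (PCS) and 0.79 (MCS). Power for 3 points is Φ(3/SE − 1.96), that is Φ(11.7) and Φ(10.3), both above 99.9%.

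**4. Sensitivity.** The practice autocorrelation across periods is not in the article and is assumed.

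| Case, after 20% attrition | Detectable, PCS | Detectable, MCS |
|---|---|---|
| 1155 recruited, autocorrelation 1 | 0.71 | 0.79 |
| 1155 recruited, autocorrelation 0.8 to 0.5 | 0.80–0.92 | 0.86–0.95 |
| 1200 recruited, autocorrelation 1 | 0.70 | 0.78 |
| 1200 recruited, autocorrelation 0.8 to 0.5 | 0.79–0.91 | 0.85–0.94 |
| 1200, worst of ICC 0.01–0.10, autocorrelation 0.5–1, ρ from 0.3 to the stated value | 1.63 | 1.51 |

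Power for 3 points stays above 99.9% in every row. It also does so with 720 recruited (PCS detectable 0.90–1.16) or 360 (1.27–1.65), taken as fewer practices of the same size.

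**The case against.** The strongest reply is that nothing is miscalculated. Every stated figure follows from the stated inputs and the named method, and the mismatch understates power. That stands: this is a choice of method that does not fit the design, not an arithmetic slip, and no recruitment or error-rate problem follows from it.

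A second reply is that 180 and 131 read as minimum requirements, that 1200 exceeds them on either reading of arm, and that 35 × 33 explains roughly where 1200 comes from. This also stands. A reader might infer that 1200 is contradicted or arbitrary; the article does not support that. What is missing is only the link between the requirement and the plan. The same sentence does point to two comparison groups, so the wording of per arm is loose rather than undefined.

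Other stronger readings also fail:

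- **The trial is underpowered.** The calculation shows the reverse.
- **The parallel formula ranks the two scores wrongly, so MCS is the limiting one.** This is true at ICC 0.02 with a constant effect, but not generally. With 1200 recruited and autocorrelation 0.5, ICC 0.05 gives 1.17 (PCS) and 1.16 (MCS), and ICC 0.10 gives 1.50 and 1.45.
- **The trial will mistake significance for relevance.** The article states its 3-point benchmark and nowhere says that significance alone will count as relevance.

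The reply does not remove the main point. The article commits itself to a method, a power and a requirement, and these belong to a different design. That is not detail left to a fuller document.

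**Conclusion.** The concern holds as a fault of justification, in the conservative direction. The 180 and 131 belong to a two-group parallel design. The planned stepped wedge has an SE of about 0.22 (PCS) and 0.24 (MCS), power above 99.9% for 3 points, and a detectable difference at 90% power of about 0.7 to 0.8, or about 0.8 to 0.95 if practice effects drift (autocorrelation 0.8 to 0.5).

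These figures rest on the article's SDs, correlations, ICC and attrition, and on three assumptions: the 9/9/9/8 split, attrition spread evenly over occasions, and the autocorrelation range. The conclusion that power far exceeds 90% survives every range tried.

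Precision for the additional duration-of-intervention analysis depends more on assumptions. For the average over exposure times, the detectable difference is about 1.1 to 1.35 if patient correlation is constant and autocorrelation is 1 to 0.6, and about 1.5 to 1.6 if patient correlation decays over time. These should be read as indicative only.

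**What to change.** Replace the calculation with one for a closed-cohort stepped wedge: 35 practices of about 33, four sequences, five occasions, period effects, practice and patient correlation, and a stated range for practice-period decay. Report the resulting power for 3 points and the detectable difference for the planned 1200. Give the requirement as a total instead of per arm, and add one sentence saying that 1200 reflects expected practice yield, if that is its origin. Any precision quoted for the duration analysis should carry its assumptions.

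The cost is a short recalculation and a rewritten paragraph. Recruitment, number of practices and measurement schedule are unchanged.

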#### Data collection

Data will be collected among older adults at home by means of computer assisted personal interviewing. For each observation, interviewers will receive training and will be supervised by research staff. A random sample of the interviews will be tape recorded; In order to enhance the quality of the data, researchers will evaluate the quality of the recordings and report back their findings to the interviewers. We will use postal questionnaires to collect data among the primary informal caregivers.

#### Analyses

First, characteristics of the participants at baseline will be described and differences between the 4 allocation arms are tested using chi-square tests and ANOVA or non-parametric tests.

Second, effect analyses will be done based on the “intention-to-treat” principle. For both older adults and their primary caregivers, all outcome measures will be compared between the group receiving the geriatric care model and the group receiving usual care using multilevel regression analysis. Multilevel regression analysis takes into account the non-independent nature of hierarchical data and does not require data for a fixed number of observations for all respondents [38]. In the present study, three levels can be distinguished. Repeated observations are clustered within the patient and the patients are clustered within the primary care practices. Potential confounding (due to baseline differences) and effect-modifying will be accounted for during the analysis. If necessary an adjustment will be made for baseline differences between the groups.

In addition to the investigation of the overall effect of the intervention, the stepped-wedge design allows us to study the effects of the duration of the intervention on outcome measures [39]. Therefore, in additional analysis, the interaction between time and intervention will be added to the analyses.

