## Methods

### Study design and setting

We will implement the geriatric care model using a stepped-wedge cluster randomised clinical trial design. A stepped wedge design is a type of cluster randomized trial design involving sequential roll-out of an intervention to primary care practices (clusters) over a number of time periods [21]. Primary care practices in the control group offer usual care, whereas practices in the intervention group deliver care according to the geriatric care model. By the end of the study, all practices will have started with the intervention. The trial will run over a 24-month period, and will be conducted among a total of 35 primary care practices in the Netherlands, with practices distributed among the regions Amsterdam (18 practices) and West-Friesland (17 practices). The Amsterdam region is of an urban nature, whilst the West- Friesland area can be characterized as an urbanised rural setting. Following participant inclusion, effect measurements will be administered at baseline and at 6, 12, 18, and 24 months (Figure 1). The study received approval by the medical ethics committee of the VU University medical centre. Participants will enrol only after a signed declaration of informed consent.

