### Randomisation

Per region, primary care practices will be randomised using the computer-based ‘Random Allocation Software’ program. In both regions, primary care practices will be allocated to one of a total of four allocation arms by randomization. The allocation arm number designates the starting moment of the intervention with the geriatric care model at practice level (at 0, 6, 12 and 18 months after baseline). Figure 1 shows the number of primary care practices per region, as well as the starting moment of the geriatric care model on cluster level.

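### Baseline differences between arms are tested as if patients had been randomised, and adjustment for them is left open without a criterion

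*Protocol article*

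**What the plan says.** Three statements in the protocol article bear on this point.

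- **Unit of randomisation (Randomisation).** "Per region, primary care practices will be randomised", to four arms that start the intervention at 0, 6, 12 or 18 months.
- **Baseline comparison (Analyses, opening paragraph).** Participant characteristics are described and "differences between the 4 allocation arms are tested using chi-square tests and ANOVA or non-parametric tests". No allowance for practice is mentioned.
- **Effect model (Analyses, next paragraph).** The effect analyses are multilevel: "Repeated observations are clustered within the patient and the patients are clustered within the primary care practices". The section then says "Potential confounding (due to baseline differences) and effect-modifying will be accounted for during the analysis" and "If necessary an adjustment will be made for baseline differences between the groups". It gives no covariate list and no rule for when adjustment becomes necessary.

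Clustering is therefore recognised for the effect analyses, and in the sample size section, but not for the baseline tests.

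**The concern.** The named tests take the patient as the independent unit. Patients in one practice resemble each other, so arm means vary more by chance than the tests allow, and chance imbalances are declared significant too often. In addition, a test of baseline difference under proper random allocation asks a question whose answer is already known.

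The second issue is the open adjustment clause. Without a criterion, the covariates in the effect model can be settled after the imbalances have been seen. Several primary models then remain possible, and the one reported may have been chosen because of noise. A reader of the trial report would also see baseline p-values that overstate how unevenly the arms were made up.

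**Working it through.** **Inputs from the protocol article (Sample size calculations):** SD 7.1 (PCS) and 6.6 (MCS); correlation of repeated measurements 0.66 and 0.5; 4 follow-up measurements; ICC 0.02; 33 patients per practice; alpha 0.05; power 90%; difference 3 points; attrition 20%. **From Study design and setting:** 35 practices (18 and 17).

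**Step 1: reproduce the plan's own figure.** Two-sided alpha is assumed; it reproduces the result.

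n = 2 × [SD × (1.960 + 1.282) / 3]² × [1 + (4 − 1) × rho] / 4

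- PCS: n = 87.7. Times the design effect 1 + (33 − 1) × 0.02 = 1.64 gives 143.8. Divided by 0.8 gives 179.8, so 180 (stated: 180).
- MCS: n = 63.6. Times 1.64 gives 104.3. Divided by 0.8 gives 130.3, so 131 (stated: 131).

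The sample size thus depends on a design effect of 1.64, which the baseline tests leave out.

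**Step 2: error rate of a patient-level four-arm test.** Under chance allocation the between-arm statistic is inflated by about the design effect (DE), so

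P(reject) ≈ P(chi-square on 3 df > 7.815 / DE).

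At DE = 1.64 this is P(chi-square on 3 df > 4.77) = 0.190. With the F critical value in place of 7.815 it is 0.189.

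**Step 3: check by simulation.** There were 20,000 runs with 35 practices of 33 patients. The arm split of 9/9/9/8 and the 30% prevalence for the binary variable are assumptions. Only the ICC of 0.02 comes from the protocol; the other ICCs are assumed.

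| ICC | DE | Formula (F) | ANOVA on patients | Chi-square on patients | ANOVA on practice means |
|---|---|---|---|---|---|
| 0.01 | 1.32 | 11.5% | 11.6% | 11.4% | 5.1% |
| 0.02 | 1.64 | 18.9% | 18.8% | 18.9% | 4.9% |
| 0.05 | 2.60 | 38.9% | 39.0% | 39.4% | 4.9% |
| 0.10 | 4.20 | 60.1% | 60.1% | 60.2% | 5.1% |

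Using 1200 / 35 = 34.3 patients per practice instead of 33 gives 19.5% at ICC 0.02. The non-parametric option was not simulated, but rank tests on patients rest on the same independence assumption.

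**Step 4: what this means for a baseline table.** With 10 characteristics, taken as independent (both assumptions), the chance of at least one false flag is 1 − 0.81¹⁰ = 88%, against 1 − 0.95¹⁰ = 40% for a test that holds its 5% level.

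**Step 5: how far this can reach the treatment effect.** Measurements fall at 0, 6, 12, 18 and 24 months. Reading baseline as before any start, every arm supplies usual-care data at baseline and intervention data at 24 months. Much of the contrast is therefore within practice, where stable baseline differences largely cancel. For region, an assumed difference of 0.5 point per 6 months in regional trend shifts the estimate by 0.002 to 0.028 point under example balanced splits (such as 5/5/4/4 and 4/4/4/5). The largest of these is 0.028 / 3, or about 1% of the 3-point target.

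**The case against.** - **The text does not tie adjustment to the tests.** Testing and adjustment stand in separate paragraphs, and necessity could mean prognostic relevance or a change in the estimate. This stands: a reader might infer that p-values choose the covariates, but no sentence says so. What remains is that adjustment is conditional on observed differences and has no criterion.
- **Region may already be in the model.** A reader might infer that it is left out, because only observation, patient and practice are named. Those are the levels of the hierarchy, not a list of fixed effects, and a condensed article may leave stratification factors to the full plan. This stands: silence does not show exclusion.
- **The four arms are the randomised groups.** A reader might infer that the tests compare the wrong groups, since each arm later contributes to both conditions. Comparing randomised arms at baseline is natural, so that criticism is not supported. The fault is in the unit of analysis.
- **Imbalance may not be pure chance.** Physicians select patients within practices, and the article does not say whether this comes before randomisation. The 19% applies to chance allocation only. Patient-level tests still could not separate selective recruitment from ordinary variation between practices.
- **The ICC of 0.02 is stated for SF-12 scores,** not for other characteristics. This stands, and is why a range is shown.
- **Analysts are blinded to group assignment (Blinding).** This limits steering towards a preferred result. It does not fix the model in advance.

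**Conclusion.** The point holds as a fault in a stated method, of modest consequence. The baseline tests have the wrong error rate: about 19% instead of 5% at the protocol's own ICC and cluster size, and about 12% to 39% for assumed ICCs of 0.01 to 0.05, all under chance allocation. The conditional adjustment clause lets the effect model depend on the imbalances observed.

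The likely harm is misleading baseline p-values and a data-dependent choice of model. A reader might go further and infer a materially biased treatment effect. The documents do not support that: much of the comparison is within practice, and no calculation here shows bias or an inflated error rate for the effect itself. The region element is only a free improvement, with an effect of at most about 0.03 point under the assumed trend and splits.

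**What to change.** In the Analyses section:

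1. Replace the baseline significance tests with a descriptive table by allocation arm.
2. Delete the conditional adjustment clause and bring the sentence on confounding before it into line. Name the adjustment covariates in advance, from prognostic baseline variables that the trial collects. Age and PRISMA-7 score are examples, since both are established at eligibility; the choice is for the trial team.
3. Include region as a two-level fixed factor, because it is the randomisation stratum. If the full plan already does this, a line of confirmation is enough.
4. Do not enter baseline SF-12 as a covariate if the baseline measurement is also part of the outcome vector.

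The cost is wording only. No data collection changes, and the stated 180 (PCS) and 131 (MCS) per arm stay as they are.

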## Discussion

The ACT-study aims to investigate the extent to which the geriatric care model has an effect on frail older adults’ quality of life. To our knowledge, it is one of the first European studies adopting a chronic care model approach to not only assess the effectiveness, but also the cost-effectiveness and the implementation process of an intervention for frail older adults living at home.

Carrying out the study in a real life primary care setting will provide insight into the generalizability of the geriatric care model, and may facilitate future implementation into routine practice. Moreover, the stepped-wedge design used in this study will allow us to introduce the intervention to all primary care practices participating in the study, so all frail older adults in the four allocation arms will eventually receive the geriatric care model. This has a number of advantages. First, the phased rolling out of the intervention will give us an opportunity to avoid having to withhold the geriatric care model from people who might benefit from it. Not only is this ethical argument compelling in itself, it has also played an important role in motivating primary care physicians to participate in the study. In addition, introducing the intervention to all four allocation arms offers methodological advantages. As mentioned in the effect evaluation paragraph, it will present us with the opportunity to take into account the effects of the duration of the intervention on outcome measures, Thus allowing us to differentiate between changes in outcomes due to time and due to the intervention.

In the years to come, the aging of the population will increasingly impose a strain on health care systems worldwide. It has become apparent that tackling emerging obstacles is essential in the securing of high-quality elderly care. By introducing the geriatric care model, we hope to contribute to the existing evidence on quality improvement and the effectiveness of integrated care models, and to present a solution for the many challenges facing care for older adults today.

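### The main effect analysis names no calendar-time effect, although exposure rises with calendar time in this stepped wedge

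*Protocol article*

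**What the plan says.** The protocol article describes the effect analysis under Analyses:

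- The main comparison: "all outcome measures will be compared between the group receiving the geriatric care model and the group receiving usual care using multilevel regression analysis".
- The random structure: "Repeated observations are clustered within the patient and the patients are clustered within the primary care practices".
- The adjustment: "Potential confounding (due to baseline differences) and effect-modifying will be accounted for during the analysis".
- Time, in the following paragraph on duration of the intervention: "in additional analysis, the interaction between time and intervention will be added to the analyses".

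The roll-out is given under Randomisation, where the allocation arm sets the "starting moment of the intervention with the geriatric care model at practice level (at 0, 6, 12 and 18 months after baseline"). Study design and setting adds: "By the end of the study, all practices will have started with the intervention". SF-12 is measured at 0, 6, 12, 18 and 24 months.

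The Discussion presents the design, through the analysis of intervention duration, as "allowing us to differentiate between changes in outcomes due to time and due to the intervention".

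**The concern.** In a parallel trial both groups are observed over the same calendar period, so a common trend cancels. In a stepped wedge it does not. Usual-care observations come mostly from early occasions and intervention observations mostly from late ones. Randomising the start time makes practices comparable but leaves calendar time unbalanced between the two conditions.

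The adjustment named in the article does not help, because the confounder is time after baseline rather than a baseline difference. Random intercepts do not help either. They move the weight towards before-and-after contrasts within a patient, and that is where a trend shows most strongly.

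Participants are frail, aged 65 or over and followed for two years, so a change in SF-12 over time that is unrelated to the care model is plausible. At stake are the primary estimate, its type I error, and the Discussion's claim that time and intervention can be told apart.

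**Working it through.** **Inputs from the protocol.** 35 practices; 33 participants per practice at baseline; attrition 20%; SD 7.1 (PCS) and 6.6 (MCS); correlation of repeated measurements 0.66 and 0.50; ICC 0.02; target difference 3 points; alpha 0.05; power 90%; starts at 0, 6, 12 and 18 months; SF-12 at 0, 6, 12, 18 and 24 months.

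**Assumptions.** Month 0 is pre-intervention in every arm. Arms hold 9, 9, 9 and 8 practices (Figure 1 is not visible). Any drift is linear and common to all arms. Practice and patient effects are random intercepts. Testing is two-sided.

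**1. The plan's own figure.** n = 2(z₀.₉₇₅ + z₀.₉₀)² · SD² · [1 + (T−1)ρ] / (T·δ²), with T = 4 and (z₀.₉₇₅ + z₀.₉₀)² = 10.507. Multiply by the design effect 1 + 32 × 0.02 = 1.64 and divide by 0.80.

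- PCS: 87.69 × 1.64 / 0.80 = 179.8, so 180.
- MCS: 63.57 × 1.64 / 0.80 = 130.3, so 131.

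Both stated figures reproduce. The formula is a two-group parallel one and contains no time term, so it does not settle how time is modelled.

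**2. Exposure against calendar time.** The share of practices on the intervention at months 0, 6, 12, 18 and 24 is about 0, 25, 50, 75 and 100%. With equal arms, the 10 usual-care arm-by-occasion cells average month 6 and the 10 intervention cells month 18. With 9/9/9/8 practices the means are 5.9 and 17.9.

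**3. Hand bounds on the leakage (equal arms).**

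- A crude pooled comparison contrasts months 18 and 6: 12/24 = 50% of a linear 24-month drift.
- A purely within-patient comparison regresses time on exposure within each arm. In 6-month units the sums of products over arms are 2 + 3 + 3 + 2 = 10. The sums of squares of exposure are 0.8 + 1.2 + 1.2 + 0.8 = 4. The slope is 10/4 = 2.5 units out of 4, or 62.5%.

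The mixed model lies between these bounds, close to the second.

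**4. Generalised least squares, no time term.** The variance components follow from the stated inputs: practice = ICC × SD², patient = (ρ − ICC) × SD², residual = (1 − ρ) × SD².

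- PCS: 1.01, 32.26 and 17.14.
- MCS: 0.87, 20.91 and 21.78.

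With 33 × 0.80 = 26.4 participants per practice:

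| | Bias per 1 point/year | Share of 24-month drift | SE without time | SE with categorical time |
|---|---|---|---|---|
| PCS | 1.23 | 61.7% | 0.135 | 0.219 |
| MCS | 1.22 | 61.2% | 0.151 | 0.244 |

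**5. Consequences over a range of assumed declines, no true effect, no time term.**

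| Decline per year | Bias PCS / MCS | Rejection PCS / MCS (nominal 5%) |
|---|---|---|
| 0.25 | −0.31 / −0.31 | 63% / 52% |
| 0.5 | −0.62 / −0.61 | 99.5% / 98% |
| 1 | −1.23 / −1.22 | about 100% |
| 2 | −2.47 / −2.45 | about 100% |

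With a true effect of +3 on PCS and a decline of 2 points per year, the expected estimate is 3 − 2.47 = 0.53. A decline of 3/1.23 ≈ 2.4 points per year would cancel the effect.

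**6. With measurement occasion in the model.** The bias from the common drift is 0, the rejection rate is 5%, and power for 3 points exceeds 99%. The power result also holds with totals of 720, 960 and 1200 participants.

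**The case against.** The strongest reply is that the omission is inferred from silence. The article condenses a fuller protocol, never lists the fixed effects, and nowhere says that time is left out. An interaction that is added to a model normally joins its main effects. The Discussion also shows that the authors had the separation of time from intervention in mind.

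Part of this stands. A reader might infer that the plan excludes calendar time from the primary model. The text does not support that: time is not named, which is different from being ruled out.

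The reply does not remove the point. The article does state the main comparison, its levels and its adjustments, and it assigns time to a secondary analysis. The added interaction implies a time main effect at most in that additional model, whereas the overall effect comes from the analysis to which the interaction is added. Time there may also mean duration of exposure, which is not calendar time. The Discussion rests its claim on that same duration analysis.

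Two further inferences go too far:

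- A reader might conclude that all secular change would be read as an intervention effect. Under a linear drift the share is about 61–62%.
- A reader might expect regression to the mean to create a false benefit. Selection is on physician-judged frailty, polypharmacy and PRISMA-7, not on SF-12, and the documents give no means of sizing such an effect.

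**Conclusion.** The point holds as a fault in how the primary comparison is specified. Fitted as written, with no period effect, the model would give a confounded estimate, and the primary comparison would not deliver the separation of time from intervention that the Discussion claims.

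The size is about 1.2 SF-12 points of bias per 1 point per year of common linear drift. If participants decline, the bias works against the care model, masking a benefit or suggesting harm.

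This is conditional on time being omitted and on a drift existing. The documents give no drift rate, so the range of 0.25 to 2.4 points per year used here is an assumption. The arm sizes and a pre-intervention month 0 are also assumed. It would be wrong to say outright that the trial's primary estimate is biased. The sample size is not threatened.

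**What to change.** State in Analyses that the primary model for each outcome contains:

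- measurement occasion as a categorical fixed effect, using the occasions at which that outcome is measured (0, 6, 12, 18 and 24 months for SF-12; 0, 12 and 24 months for CANE, following Table 1);
- the practice's time-varying exposure indicator;
- random effects for patient and practice.

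Report the exposure coefficient from this model as the overall effect. Keep time since the start of the intervention as a separate variable for the additional analysis of duration. A linear time term would also remove a linear drift, but the categorical form protects against non-linear change as well.

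The cost is a sentence or two of text and some precision: the standard error rises from 0.135 to 0.219 (PCS) and from 0.151 to 0.244 (MCS). Power for 3 points stays above 99% on the protocol's inputs and the random-intercept structure used here.
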